#### Predictors-moderators

##### Autism Characteristics

The Dutch Autism-Spectrum Quotient-10 (AQ-10 [55]; is used to measure autism characteristics. The AQ-10 consists of 10 items scores on a 4-point Likert scale, determining one’s difficulties with social skills, routine, imagination, detail-focus, and attention switching. The total score ranges from 0-10, with a higher score indicating more autistics traits. A score of 6 or higher is indicative for a full diagnostic assessment [56]. The internal consistency of the AQ-10’s total score is high (α = .85 [57];). The AQ-10 is able to distinguish between individuals with and without a clinical diagnosis of ASD [56].

##### Childhood Trauma

The Childhood Trauma Questionnaire – short form (CTQ-SF [58];) is used to assess the severity of childhood maltreatment. The short form consists of 25 items that are depicted to measure 5 subscales of childhood trauma: physical, sexual, and emotional abuse and physical and emotional neglect. Answers are measures on a 5-point scale ranging from 1 (never true) to 5 (very often true), resulting in a total score of the subscales between 25-125, with higher scores reflecting more childhood trauma. The total score of the subscales will be tested as predictor and moderator of treatment effects. A Dutch validation study showed that the CTQ-SF has a good internal consistency (Cronbach’s alpha > .87 for the separate scales) and showed a good convergent validity with scores on a semi-structured interview for childhood trauma [59].

##### Verbal Intelligence (NLV)

Verbal intelligence is assessed by the Dutch version of the National Adult Reading Test (NLV [60];). For this test a list of 50 words with an uncommon pronunciation is read out loud by the patient. For every correct pronunciation 2 points are awarded, for every unclear or questionable pronunciation 1 point is given, and for incorrect pronunciation no points are given. The total score consists of the aggregated points.

##### Demographics

A semi-structured demographical interview will be used to collect some general patient characteristics. The age, gender, marital status, sexual orientation, ethnic and cultural background, level of education, employment situation, previous psychological treatments, among other things, will be assessed.

##### Analyses

All analyses are planned to be carried out by SPSS or R statistical software and Excel (for Bootstraps).

Primary and secondary outcomes are analysed with Linear Mixed Models (LMM), with random effect of site. As data of group members are not independent because group members might influence each other, this dependency needs to be taken into account. With the semi-closed group format, groups change in composition every 10 sessions, and participants will share different amounts of time in sessions with group peers: from all group sessions to 10 group sessions. It is plausible to model covariances as a function of the amount of time (i.e., sessions) patients have spent together in a group. This can be achieved in a multilevel model with repeated measures by specifying a Toeplitz covariance structure to model this dependency on the group level. In case this Toeplitz structure turns out to be unsuitable to model the dependency, another (less complex) structure will be specified. For the repeated part at the individual level, the best fitting covariance structure will be chosen (e.g., AR1, ARMA11, Unstructured). If residuals deviate substantially from normal distribution, Generalized LMM (GLMM) will be used with an appropriate distribution (e.g., negative binomial or gamma in case of skewed distributions). All analyses are conducted on the basis of intention-to-treat and will be controlled for initial symptom severity. Dropout from treatment will be analysed with GLMM survival analysis with site as random effect. To take into account participants’ potential influence on each other in group treatment, again a Toeplitz covariance structure will be specified to model this dependency unless a different structure turns out to be more suitable. The three arms will be mutually compared, with a primary interest in the GST-TAU and the GST-IST comparisons. Although the IST-TAU difference is not part of the main research questions, this difference will be analysed exploratively. Tests of predictors and moderators (sleep quality, introversion, autism traits, childhood trauma, verbal intelligence, demographic characteristics) will be done by similar (G)LMM analyses, with the predictor, predictor x time, predictor x treatment, and predictor x time x treatment interactions added to the model.

To derive a tool that informs future patients and therapists what treatment is likely to be most efficacious for the specific patient (personalized care), we currently plan to use the Personalized Advantage Index (PAI) procedure developed by DeRubeis [61]. The LMM model of the outcome analysis is the starting point. Then, potential predictors and moderators are derived by suitable predictive machine learning models. Two methods for model selection, best subset selection and Lasso regression, will be performed and validated using 10-fold cross validation, after which one of the two methods will be selected. The individual’s PAI and hence the advantage of optimal treatment allocation can be estimated with a leave-one-out procedure [61, 62]. However, the field of personalized treatment allocation is developing rapidly and other methods might turn out to be more accurate and robust than the PAI method. We will therefore use a method that is optimal given the state of affairs at the end of data collection.

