The power analysis is based on 9 sites, despite 10 sites intent to participate, because sites might withdraw or not reach the intended N. For feasibility purposes a larger N is intended for the GST condition, as more participants can be treated at the same time in a group. With minimal N’s of 162 (GST), 108 (IST) and 108 (TAU) power of pairwise comparisons GST-IST and GST-TAU is 90% at an adjusted p-level of .025 to detect an effect size of d = .44 at post-test (or follow-up). For the GST-IST comparison, we don’t have expectations about the direction of a possible difference, but the power is sufficient to detect a medium effect size. One potential issue is treatment dropout. For pairwise comparisons of GST with the other two arms power is 80% to detect an RR = 2.5 at adjusted p = .025, for instance when dropout is 25% from GST vs. 10% from IST). (G)LMM analysis for repeated measures will be used to account for correlations introduced due to grouping (at multiple levels) and compensate for potential loss of power due to treatment drop-out. This type of analysis usually has greater power compared to non-multilevel/non-repeated measures analyses, however an actual power calculation for multilevel analysis with repeated measures and multiple sites is very difficult if not impossible because of the many random effects of the to-be-estimated model.

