### Therapists, Training and Supervision

Schema therapists, individual as well as group, are required to have followed the basic ST 25-hour training and have completed at least 10 supervisions whilst continuing supervision. In addition, GST therapists are required to have followed a 4-day Farrell & Shaw GST training as well as a 1-day training in the GST-CLC protocol by two skilled trainers [29]. Every GST group is conducted by two schema therapists and has a designated stand-in therapist who can replace the standard therapists when they are absent. This stand-in therapist needs to adhere to most of the aforementioned requirements except for having followed the 4-day F&S GST training. Therapists for the IST are also required to be either a junior schema therapist registered at the Dutch schema therapy association (VST) or in training to become one with accompanying continued supervision and a minimum of 10 supervisions completed. Additionally, IST therapists need to follow a 1-day training by one of the current authors [name] in the IST protocol. It is possible for a schema therapist to be a GST as well as IST therapist, if they meet requirements for both treatment conditions.

Both GST and IST therapists engage in weekly peer supervision sessions at their site. GST and IST therapists are allowed to have these together. For the GST condition, each institute will receive up to 10 supervision sessions of 50 minutes by one of the creators of the GST CL-C protocol during the course of treatment (on average about once every two to three months). For IST two-hour online supervision every 6 months is offered for therapists who want to discuss specific issues. Such supervision is available to all sites. For the TAU condition no requirements are formulated regarding the training or supervision of therapists, as the treatments in this condition vary greatly and this condition is meant to reflect practice as usual at the institute. Therapists’ experience and credentials are gathered by a questionnaire designed specifically for trial therapists.

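### The outcome and dropout models have no therapist term, so same-therapist patients in IST and individual TAU are independent given site; if therapists work mainly in one arm, standard errors are somewhat too small

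*Protocol article*

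**What the plan says.** The Analyses section fixes the dependency structure in three parts.

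- Site: "Primary and secondary outcomes are analysed with Linear Mixed Models (LMM), with random effect of site".
- Group: the reason given is influence between peers, "As data of group members are not independent because group members might influence each other, this dependency needs to be taken into account". The form is a function of shared time, "It is plausible to model covariances as a function of the amount of time (i.e., sessions) patients have spent together in a group", achieved by "specifying a Toeplitz covariance structure to model this dependency on the group level". If that proves unsuitable, a simpler structure replaces it for the same dependency.
- Patient: a best-fitting covariance for the repeated measures.

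The dropout model repeats site plus the group structure. Neither model names a therapist level.

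On delivery, IST is individual. TAU mixes individual and group therapies, and "For the TAU condition no requirements are formulated regarding the training or supervision of therapists". GST groups are led by two therapists. On overlap between the schema therapy arms, "It is possible for a schema therapist to be a GST as well as IST therapist" if both sets of requirements are met. The Discussion lists therapists among the site characteristics that can influence outcomes and answers this with variance modelled at site level. It also says that therapist characteristics may be entered into later analysis.

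The Sample size section plans "162 (GST), 108 (IST) and 108 (TAU") patients and states that "power of pairwise comparisons GST-IST and GST-TAU is 90% at an adjusted p-level of .025 to detect an effect size of d = .44".

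**The concern.** The plan treats dependence between patients as a validity matter in group treatment but gives the individual treatments no dependence below site. On the 9-site basis used for power there are about 12 IST and 12 TAU patients per site. Unless each therapist treats only one of them, some share a therapist.

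A site intercept common to all arms cancels from a within-site comparison of arms. It therefore cannot absorb differences among therapists who work in only one arm. Those differences stay in the GST-IST and GST-TAU contrasts but are missing from their standard errors. In that situation, chance differences between a few therapists can be reported too readily as differences between therapies.

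Therapist characteristics entered as covariates would explain part of this variation at most. They do not make same-therapist patients correlated in the model.

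**Working it through.** **Inputs from the article.** Arms of 162, 108 and 108; d = .44; level .025; 9 sites, hence 162/9 = 18 GST and 108/9 = 12 patients per comparator arm at each site; six cohorts per site with three GST patients each; 30 group sessions, with turnover every 10.

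**Assumptions, not in the article.** Therapist ICC .02 to .08; m = 3 to 6 patients per comparator therapist; therapists nested in arm. For GST-TAU the figures also take all TAU as individually delivered, because the split is not stated.

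**1. The plan's own figure.** With independent patients and unit SD, the contrast variance is 1/162 + 1/108 = 0.01543, so SE = 0.1242. Two-sided .025 gives z = 2.2414. Power = Φ(.44/0.1242 − 2.2414) = Φ(1.30) = .903. The stated 90% reproduces, with no allowance for clustering.

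**2. Clustering in the comparator arm only.** This takes GST dependence as fully handled by the peer term.

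Variance = 1/162 + [1 + (m − 1)ICC]/108. Ratio = √(variance/0.01543). Error = 2[1 − Φ(2.2414/ratio)].

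| ICC | m | True/modelled SE | Error at nominal .025 | Power |
|---|---|---|---|---|
| .02 | 3 | 1.012 | .027 | .90 |
| .05 | 6 | 1.072 | .037 | .86 |
| .08 | 3 | 1.047 | .032 | .87 |
| .08 | 6 | 1.114 | .044 | .83 |

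The power column uses the true SE with the critical value 2.2414. A caseload outside the assumed range, one therapist for all 12 comparator patients at a site, gives a ratio of 1.153 and error .052 at ICC .05.

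**3. GST patients who share no session.** Six cohorts of three give 18 patients and 18 × 17/2 = 153 pairs per site. A patient stays for 30 sessions and new patients enter every 10, so cohorts 0, 1 or 2 intakes apart overlap. Pairs that overlap: 6 × 3 + 5 × 9 + 4 × 9 = 18 + 45 + 36 = 99. The other 54 never meet, an average of 2 × 54/18 = 6 per patient. If the peer term covers the 99 pairs, and the 54 share a therapist pair whose effect is unmodelled, the GST factor is 1 + 6·ICC:

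| ICC | m | Variance | Ratio | Error |
|---|---|---|---|---|
| .02 | 3 | 1.12/162 + 1.04/108 = 0.01654 | 1.035 | .030 |
| .05 | 6 | 1.30/162 + 1.25/108 = 0.01960 | 1.127 | .047 |
| .08 | 6 | 1.48/162 + 1.40/108 = 0.02210 | 1.197 | .061 |

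**4. Check by simulation.** The design was 9 sites with 18 GST and 12 IST patients each, a single post-test, a site-stratified analysis without a therapist term, and 8,000 runs per scenario. With three IST therapists per site, IST clustering only and ICC .02 to .10, error was about .028 to .043.

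**5. The same therapists in GST and IST.** When the same therapists treated both arms at each site, the simulated modelled-to-true SE ratio was 1.01 to 1.05 for ICC .02 to .10. The GST-IST standard error is then not understated.

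**The case against.** **The article may not list every random effect.** The Sample size section speaks of grouping at multiple levels and of many random effects, and a condensed article may leave the full list to an analysis plan. But the Analyses section does set out a structure, and the Discussion says where therapist differences go, namely to site level. Neither general remark names a therapist level. The point stands against the text as published.

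**The direction depends on conditions.** A reader might infer that both primary tests are anti-conservative as written. The documents do not support that. It needs a therapist ICC above zero and therapists working mainly in one arm, and neither is documented. Overlap between GST and IST is allowed, and full overlap removes the problem for that contrast. Nothing is said about overlap with TAU.

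**Same-therapist patients are not wholly independent in the model.** They share the site effect. The independence is conditional on site.

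**GST is the weakest part.** A reader might count all 17 fellow GST patients at a site as unmodelled, which would put the error at .037 to .093. That ignores the 99 of 153 pairs that share sessions and fall under the peer term. Even for the other 54, an unbanded Toeplitz or the fallback structure could absorb part of a common therapist-pair effect.

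**The size rests on assumed values.** This is correct. With 3 patients per comparator therapist, the error is only .027 to .032 across the ICC range.

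**Conclusion.** The point holds in conditional form. The published models contain no therapist dependence for IST or individually delivered TAU, and a site effect cannot supply it. With therapists nested mainly in arm, ICC .02 to .08 and 3 to 6 patients per comparator therapist, the true standard error is 1 to 11% larger than modelled, and a nominal .025 test has error of about .027 to .044. Adding an unmodelled therapist-pair effect for GST patients who never met raises this to about .030 to .061, or less to the extent that the group structure absorbs it.

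The stated 90% power is not an arithmetic error. It is the figure for independent patients. The effect is modest under most of these assumptions, but it touches both primary contrasts and is cheap to address, so the change should be made.

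**What to change.** Record the treating therapist or therapists for each patient. In the outcome and dropout models:

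- add a therapist random effect within site for IST and individually delivered TAU;
- keep the shared-session covariance for GST;
- use a group-level term for group TAU;
- where a therapist works in both GST and IST, use individual therapist identifiers with crossed or multiple-membership effects. A therapist-pair identifier cannot link a GST patient to the same person's IST patients.

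If the therapist variance cannot be estimated, report a sensitivity analysis of both primary contrasts with the therapist ICC fixed at .02, .05 and .08.

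The cost is the therapist identifiers for each patient, slightly wider intervals and some convergence work, most of it where multiple membership is needed. Trial therapists already complete a questionnaire on experience and credentials, so the added data collection is small.

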A popular and economically attractive form of ST is group treatment, as larger numbers can be treated in less therapist time than with individual therapy (>50%), making it potentially more cost-effective than IST. In addition, the group format might offer extra therapeutic advantages such as support and understanding from group members which can help patients gain a sense of belonging and can facilitate secure attachment. Possibly group therapy would be exposure in itself for patients with cluster-c PD, where social avoidance and dependence play a major role in their pattern of symptoms. Furthermore, group therapy can induce vicarious learning and offer in vivo opportunities to practice with setting boundaries and expressing one's needs in a healthy way [16]. Group schema therapy (GST) has proven to be an effective treatment for borderline PD [17, 18] and was found superior to TAU [19, 20]. Only two studies have investigated GST for Cluster-C PD. First, a modest pilot study of a GST-protocol including 8 patients with mixed personality disorders (6 patients with avoidant PD and 2 with borderline PD) showed significant decline in avoidant PD symptom severity at follow-up [21]. The two patients with borderline PD were both reported as dropout, suggesting that mixing different PDs within this GST-protocol may be contra indicative. Second, a larger pilot study investigated our current GST-protocol in a multicenter open trial (9 sites, 137 patients). The treatment was highly acceptable: only 16 dropouts (11.6%). The decrease in symptoms from baseline to follow-up of the primary PD was large (effect sizes ranged from cohen’s d = .59 for obsessive compulsive PD, d = 1.33 for avoidant PD and, d = 1.52 for dependent PD).

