### Randomization

Randomization of the participants is conducted by an independent researcher after completion of the baseline assessment. Computerized covariate adaptive randomization is used, considering the primary diagnosis and gender. Six cohorts per site are planned, randomized approximately every 10 working weeks. It is possible that sites where inclusion runs smoothly will end up doing more cohorts relative to sites where inclusion falls behind. To guarantee balanced conditions over time, the aim is to randomize cohorts of 7 participants at a time per site resulting in GST (n=3), IST (n=2) and TAU (n=2). As participant influx may vary from time to time, occasionally less or more than 7 participants may be randomized. The distribution over the 3 conditions then will depend on 1) the capacity at the site in question, or 2) the need to allocate more participants to 1 particular condition in order to maintain the overall 3:2:2 distribution. At least 3 participants will be randomized per cohort as to ensure a chance for each participant to end up in one of the 3 conditions. The assigned intervention will be revealed to the patient in the first treatment session by the therapists.

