### Evaluation of Clinical Effectiveness

#### Primary outcome measures

##### Cluster-C Personality Disorder Severity Indices

Primary outcome is severity during the last month of the primary PD. For each Cluster-C PD a severity interview will be administered, assessing frequency of different manifestations of the pertinent PD as defined by the DSM-5 (Avoidant Personality Disorder Severity Index (AVPDSI [33];); Dependent Personality Disorder Severity Index (DPDSI [34];); Obsessive Compulsive Personality Disorder Severity Index (OCPDSI [35];). The AVPDSI consists of 53 questions divided into 7 subsections reflecting the 7 PD criteria. For each question both avoidance and fear over the past month are rated on a scale from 0 (never) to 5 (every day). The average avoidance per subsection and the average fear per subsection is calculated and summed up to form a total average avoidance and a total average fear score. The DPDSI consists of 47 questions divided into 8 subsections reflecting the 8 PD criteria, scored on a scale of 0 (never) to 5 (every day) over the past month. At the end of each subsection 2 additional questions are asked regarding the overall burden and impact of the subsection symptoms on a scale of 1 (not at all) to 10 (unbearably much). This results in a total sum of the average symptom scores per subsection, an average burden score and an average impact score. The OCPDSI is scored similarly, with 51 questions divided into 8 subsections reflecting the 8 PD criteria, scored on a scale of 0 (never) to 5 (every day) over the past month. At the end of each subsection again 2 additional questions are asked regarding the overall burden and impact of the symptoms on a scale of 1 (not at all) to 10 (unbearably much). This results in a total sum of the average symptom scores per subsection, an average burden score and an average impact score. These interviews have excellent interrater agreement (ICC>.90) and internal consistency (Cronbach a > .90) and are sensitive to change. By standardizing the raw scores (dividing by the baseline SD) the scores on the three instruments are converted into one severity score.

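### Arms are balanced on primary diagnosis and gender, but the outcome model described names neither; standard errors come out somewhat too wide and the tests conservative

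*Protocol article*

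**What the plan says.** **Randomisation section.** "Computerized covariate adaptive randomization is used, considering the primary diagnosis and gender". Cohorts of seven per site are the aim, split 3:2:2. If a cohort has another size, "The distribution over the 3 conditions then will depend on 1) the capacity at the site in question", or on the need to restore the overall ratio.

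**Analyses section.** "Primary and secondary outcomes are analysed with Linear Mixed Models (LMM), with random effect of site". A Toeplitz structure for dependency between group members and a repeated-measures covariance structure follow. The adjustment is given in one sentence: "All analyses are conducted on the basis of intention-to-treat and will be controlled for initial symptom severity". Gender can enter only as a demographic characteristic in the separate predictor models: "Tests of predictors and moderators (sleep quality, introversion, autism traits, childhood trauma, verbal intelligence, demographic characteristics) will be done by similar (G)LMM analyses". Primary diagnosis is not in that list either. It does appear elsewhere, among the variables for the treatment-recommendation tool (This study) and as a topic of interest (Discussion).

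**Primary outcome section.** Each patient is scored on the instrument for his or her own disorder. "By standardizing the raw scores (dividing by the baseline SD) the scores on the three instruments are converted into one severity score". No mean is subtracted.

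**Background.** Pilot change from baseline to follow-up under group schema therapy was d = 0.59 for obsessive-compulsive PD, "d = 1.33 for avoidant PD and, d = 1.52 for dependent PD".

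**The concern.** Balancing the arms on a prognostic factor removes that factor's contribution from the sampling variation of the arm difference. A model that omits the factor still counts it as residual noise. The reported standard error then exceeds the true one, p-values are too large, and some power is lost.

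Baseline severity does not stand in for diagnosis here. The pilot differences are differences in change, and one common baseline slope cannot represent three diagnosis-specific courses.

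The scaling adds a second route. Without centring, the instruments may keep different means in the pooled score. Those offsets then enter both the outcome and the baseline covariate, and the slope mixes differences between instruments with severity within an instrument.

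At stake are the precision and the true level of the two main comparisons, group schema therapy against TAU and against individual schema therapy.

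**Working it through.** **1. The plan's own figure.** Inputs from Sample size: 162 vs 108, d = 0.44, adjusted level 0.025, taken as two-sided (critical value 2.2414).

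- k = 1/162 + 1/108 = 0.01543; √k = 0.1242
- Power = Φ(0.44/0.1242 − 2.2414) = Φ(1.300) = 0.903

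The stated 90% is reproduced. It is a plain two-sample figure with no covariates.

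**2. Assumptions, because the documents give no figures.** Shares avoidant/dependent/obsessive-compulsive of 60/15/25%; baseline–post correlation r = 0.5 within diagnosis; pilot changes 1.33/1.52/0.59 in every arm; arms balanced on diagnosis.

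**3. Centred score, diagnosis in the model.** Residual variance = 1 − r² = 0.75. SE = √(0.75 × 0.01543) = 0.1076. Power = Φ(0.44/0.1076 − 2.2414) = Φ(1.849) = 96.8%.

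**4. Centred score, diagnosis omitted.**

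- Mean change = 0.60×1.33 + 0.15×1.52 + 0.25×0.59 = 1.174
- Between-diagnosis variance = 0.60×0.1565² + 0.15×0.3465² + 0.25×0.5835² = 0.118
- Model SE = √((0.75 + 0.118) × 0.01543) = 0.1157
- The true SE stays at 0.1076, so the ratio is 1.076
- Null rejection = 2 × [1 − Φ(2.2414 × 1.076)] = 1.6%
- Power = Φ((0.44 − 2.2414 × 0.1157)/0.1076) = Φ(1.679) = 95.3%

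A simulation with minimisation and site effects (400 runs) agrees: mean model SE 0.116 against an empirical 0.104 to 0.108, null rejection 1.5%, power 95.0%. With diagnosis and gender it gave SE 0.107, 2.2% and 96.0%.

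**5. Uncentred score.** Let the instrument means lie at assumed offsets, in SD units. Write C(x, y) for the share-weighted covariance across diagnoses, o for the offsets and p = o − change for the post means.

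- Common slope b = (r + C(o,p))/(1 + C(o,o))
- Model residual variance = 1 + C(p,p) − b(r + C(o,p))
- True variance under balance = 1 − 2br + b²

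For offsets 2/2/3: C(o,o) = 0.1875, C(o,p) = 0.333, C(p,p) = 0.597. So b = 0.833/1.1875 = 0.702, model variance = 1.012 and true variance = 0.791.

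| Scenario, diagnosis omitted | Model SE | True SE | Ratio | Null rejection | Power at 0.44 |
|---|---|---|---|---|---|
| Centred | 0.116 | 0.108 | 1.08 | 1.6% | 95.3% |
| Centred, half the pilot spread | 0.110 | 0.108 | 1.02 | 2.2% | 96.5% |
| Offsets 2/2/3 | 0.125 | 0.110 | 1.13 | 1.1% | 92.6% |
| Offsets 3/3/2 | 0.109 | 0.108 | 1.01 | 2.4% | 96.6% |
| Diagnosis in the model | 0.108 | 0.108 | 1.00 | 2.5% | 96.8% |

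The offsets can raise the loss (2/2/3) or nearly remove it (3/3/2).

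**6. Other shares.** The shares above average 1.17, while Sample size gives 1.24 overall for the pilot. Shares of 76.5/9/14.5% average 0.765×1.33 + 0.09×1.52 + 0.145×0.59 = 1.24. The between-diagnosis variance is then 0.0745 and the centred model SE √(0.8245 × 0.01543) = 0.113, or 4.9% too wide. By the same formulas null rejection is 1.9% and power 95.9%.

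**The case against.** **The text does not exclude diagnosis.** It says that the analyses control for initial severity, not that they control for nothing else. This is an article, and a full covariate list may stand in an analysis plan that is not shown. That is fair, and a reader should not infer a decision to leave diagnosis out. But the article describes the model in some detail and states its adjustment, and that adjustment does not match its own randomisation. The point concerns what is written.

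**The power loss is minor.** This stands. At the design effect both models exceed 90% in all the scenarios tabulated above. Larger gains can be shown at smaller effects: about 60% against 70% at 0.30 SD, in one uncentred scenario. The trial is not powered for that effect.

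**The gradient is uncertain.** The pilot had group schema therapy only. No document gives change by diagnosis under TAU or individual schema therapy, and the diagnosis shares are assumed. This stands and limits confidence in the size, though not in the direction.

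**Two stronger readings are not supported.** A reader might infer that the loss is worst on the uncentred score. That depends on instrument means that the documents do not give, and with offsets 3/3/2 the uncentred score does better than the centred one. A reader might also infer that the varying cohort split widens the standard errors. It does not: its risk is bias if outcomes drift over time. In an illustration with the group share rising from 2/7 to 4/7 over six cohorts and a drift of 0.2 to 0.4 SD, the bias was about 0.03 to 0.06 SD without a cohort term and about 0 with it. The article describes no such pattern. It calls departures from seven occasional, and one of its two rules serves to restore 3:2:2.

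**Conclusion.** The model as written omits both balancing factors. One of them, diagnosis, appears prognostic on the article's own pilot figures; for gender the documents give no such figure. The consequence is conservative: standard errors about 5 to 15% too wide and null rejection of roughly 1 to 2% instead of 2.5%. Power at d = 0.44 is about 93 to 97%, against 96 to 97% with diagnosis included. These sizes rest on assumed diagnosis shares, r = 0.5 and the pilot gradient in all arms. The loss is about 2% in SE if the spread is half the pilot's, and about 1% under some instrument offsets.

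It would be wrong to conclude that the trial is underpowered, that its 90% figure is in error, or that leaving out diagnosis inflates false positives or biases the treatment effect. The change is worth making because it is nearly free and brings the analysis into line with the design.

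**What to change.** - Add primary diagnosis, with its interaction with time, and gender as fixed effects in the primary and secondary mixed models. Add both factors to the dropout model as well.
- Define the severity score as (score − baseline mean)/baseline SD, separately for each instrument. Alternatively, keep the present scaling and state that the diagnosis terms absorb the offsets between instruments.
- Separately, consider a cohort or calendar-period term as a sensitivity analysis against drift where the arm split departs from 3:2:2. Keep it out of the primary model: 378/7 = 54 cohorts beside site and overlapping therapy groups would be a heavy random structure.

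Diagnosis and gender are already collected. The cost is a few sentences and a handful of model terms with 378 patients. Fix the choice before outcome data by arm are seen, so that the covariates are not chosen on the results.
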